**Fig 1 pone.0294131.g001:**
[figure not shown]
SPIRIT diagram. *Time-points of the protocol: *-t*_*1*_, enrolment; *t*_*0*_, baseline; *t*_*2*_, 2 weeks after baseline, start of energy restriction; *t*_*6*_, 4 weeks in energy restriction; *t*_*10*_, 8 weeks in energy restriction; *t*_*14*_, 12 weeks in energy restriction; *t*_*18*_, 16 weeks in energy restriction; *t*_*26*_, 8 weeks in neutral energy balance; *t*_*78*_, 52 weeks in weight maintenance.

The study was approved by the Ethics Committee of the Faculty of Nutrition and Food Sciences, University of Porto (Approval Number 31/2021/CEFCNAUP/2021) and will be conducted in accordance to the declaration of Helsinki for human studies from the World Medical Association [33]. It has been registered at www.clinicaltrials.gov (NCT05184361) prior to participants’ recruitment.

All participants will be informed about the possible risks of this investigation before giving informed consent for enrollment in the study. Participants´ privacy and confidentiality will be ensured, during and after investigation, in accordance with the legislation in force.

### 2.2. Sample recruitment and selection

A total of 74 women with the identified criteria (Table 1) will be selected.

**Table 1 pone.0294131.t001:** Eligibility criteria.

**Inclusion criteria**
Female sex; BMI 30–39.9 kg/m^2^; Age 20–45 years; Weight stable (less than 5% of weight variation in the past 6 months); Inactive (less then 150 min/week of moderate PA or 75 min/week of vigorous PA [34]); Living in Lisbon metropolitan area; Available to be randomized to any of the trial groups; Willing to commit with the assigned group protocol, and being available for the 8 evaluations.
**Exclusion criteria**
Previous or present major health disorders: cancer, autoimmune, chronic intestinal inflammatory, cardiac, psychiatric, kidney, and liver diseases (except liver steatosis), diabetes, or other medical conditions affecting energy balance; Menopause; Hormonal/thyroid disorders; Schizophrenia, bipolar disorder, or other psychotic disorders; Eating disorders; Major depression; Medications promoting weight gain or altering EB, including corticosteroids, antidepressants, anxiolytics, mood stabilizing, and antipsychotics; Medicines/dietary supplements for weight-loss in the previous 3 months; History of bariatric surgery/liposuction procedures; Pregnant for the previous 6 months/breastfeeding; Planning to get or getting pregnant in the next 2 years; Surgery/hospital admission in the previous month. Current consumption of more than 14 alcoholic drinks per week or abuse of other substances, and/or current acute treatment/rehabilitation program for alcohol/substance abuse.

The disclosure of the clinical trial occurred after its registration in https://clinicaltrials.gov/, and was publicized in the media and social networks. Evaluations and consultations will be taken place at the Exercise and Health Laboratory, CIPER, Faculty of Human Kinetics, Lisbon, Portugal.

### 2.3. Screening process

Screening process will be phased, to identify and recruit eligible participants and give all the necessary information for an informed consent. During this process, procedures will be detailed, motivations accessed, and expectations anticipated (Table 2).

**Table 2 pone.0294131.t002:** Screening process overview.

**Screening step 1—email and/or phone evaluation**
Provide general information about the study; Screen eligibility criteria.
**Screening step 2—online one-to-one interview**
Validation of the eligibility criteria and all the information provided in screening step 1; Assess weight loss motivation; Assess lifestyle logistics (home, work, leisure, planned holidays); Provide detailed information about the study goals, procedures, timing of evaluations, length of the intervention and weight management phase; Confirm availability for being present at the clinical trial 8 evaluation moments; Assess food preferences, food intolerances and allergies, as well as food habits using a 24h-dietary recall on weekdays and weekend; Discuss the nutritional intervention and recommendations; Ensure availability for being randomized to any of the two groups; Clarify any questions participants may have; Provide one copy of the informed consent; Schedule the 1^st^ visit/evaluation of the study.

### 2.4. Randomization

Participants will be randomized to one of the two arms of the study through a simple automatic randomization scheme generated by computer, controlled by the researcher responsible for the data treatment (which is not the main investigator). Randomization will be performed before the 1^st^ visit/evaluation. Participants will be informed of their assigned group during the 1^st^ visit/evaluation.

### 2.5. Calculation of energy stores

Considering the principle of energy conservation [5, 35, 36], the rate of change in body energy storage (ES) is equal to the difference between the rates of energy intake (EI) and EE, expressed as energy per unit of time [35].

EB equation is the following:

$$\text{ES}\;\left(\text{kcal}{\text{.d}}^{-1}\right)=\text{EI}–\text{EE}.$$

When the EI surpasses the EE, changes in ES will be positive, leading to a positive EB. On the other hand, a negative EB will be created when the EI is lower than the EE.

EB can be calculated from the change in body energy stores from the beginning to the end of the WL intervention. Therefore, using the established energy densities of 1.0 kcal.g^-1^ for FFM and 9.5 kcal.g^-1^ for FM, the following equation will be used to quantify the average rate of changed body energy stored or lost in kilocalories per day:

$$\text{EB}\left(\text{kcal}/\text{d}\right)=1.0\frac{\Delta FFM}{\Delta t}+9.5\frac{\Delta FM}{\Delta t},$$

Where ΔFFM and ΔFM represent the change in grams of FFM and FM, respectively, from the beginning to end of the intervention and Δt is the time length of the intervention in days [37–39].

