## 2. Methods

### 2.1. Study design

The BREAK study is a RCT (allocation ratio of 1:1) that will be performed in adult women with obesity, randomly divided in 2 parallel groups: 1) CER and 2) IER. This study will include a three-phase intervention:

2 weeks of neutral EB;Active WL phase, where both groups will undergo 16 weeks of ER: CER—16 weeks of continuous ER; IER—2 weeks of ER interspersed with 1 week in EB, leading to a total of 23 weeks. IER length is 7-week longer than CER due to the 7x1-week of neutral EB, to maintain the same magnitude of ER in both interventions;8 weeks in neutral EB.

Participants will also be evaluated 12 months after the 3rd phase, to determine WL maintenance success. SPIRIT diagram is presented in Fig 1.

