#### 2.6.2. Energy restriction for weight loss

For both groups, an ER of 33% of one’s DER will be created [6, 32] to achieve WL. Participants will have their personalized dietary plan adjusted every 4 weeks during the ER phase, according to REE measurements and PA monitoring, to assure the same energy deficit throughout this phase.

During this phase, participants will continue to track their weight daily at home [43, 44], and weekly share with the main investigator their overnight fasting body weight.

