#### 2.6.4. Adherence to diet

Participants from both groups will undergo an ER meeting 33% of their DER.

Adherence will be assessed through the following equation proposed by Racette et al [46]:

$$Adherence_{\left(\%\right)}=\;100\;\times \;\left[\left(1-\frac{EI_{4mo}}{EI_{baseline}}\right)\times \;\frac{100}{ER_{prescribed\left(\%\right)}}\right]$$

Where the EI will be calculated by the “intake-balance method” [47], through changes in FM and FFM, together with total daily EE (TDEE). The following equation was used:

$${\text{EI}}_{\left(\text{kcal/d}\right)}={\text{EE}}_{\left(\text{kcal/d}\right)}+{\text{EB}}_{\left(\text{kcal/d}\right)},$$

Where EE represents the total daily EE measured by accelerometry, and EB calculated through changes in FM and FFM. The degree of ER during the WL phase will also be calculated through this equation. It will be also assessed if participants from IER group not only accomplished the prescribed ER but also if underwent the 1-week periods of neutral EB.

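### Read as written, the adherence equation averages the IER deficit over 23 weeks but scores it against the full 33% prescription, so equal compliance scores about 26 to 30 points lower in IER than in CER

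*Protocol article*

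**What the plan says.** Section 2.5 sets the interval for the energy-store calculation: "EB can be calculated from the change in body energy stores from the beginning to the end of the WL intervention". The divisor, Δt, "is the time length of the intervention in days". No value is given by arm.

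Section 2.1 gives the length of the weight-loss phase. For one arm it is "CER—16 weeks of continuous ER"; for the other, "IER—2 weeks of ER interspersed with 1 week in EB, leading to a total of 23 weeks". It adds that "IER length is 7-week longer than CER due to the 7x1-week of neutral EB", and gives equal restriction in the two arms as the reason.

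Section 2.6.1 prescribes 100% of daily energy requirement (DER) in energy-balance periods. Section 2.6.2 prescribes a 33% restriction to both groups, with the plan reset as requirements change: "Participants will have their personalized dietary plan adjusted every 4 weeks during the ER phase".

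Section 2.6.4 computes energy intake (EI) as EE plus energy balance (EB). It puts EI into one adherence formula for both arms, with a numerator EI labelled 4mo, a baseline EI and the prescribed restriction, which the section gives as 33% for both groups. It also says: "The degree of ER during the WL phase will also be calculated through this equation".

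**The concern.** The top and bottom of the adherence ratio refer to different stretches of time in the IER arm. The deficit is averaged over 16 restricted and 7 unrestricted weeks. The prescription it is compared with applies only to the 16 restricted weeks. In CER the two coincide. Identical compliance therefore gives different scores by arm.

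At stake is the reading of adherence and of achieved restriction by arm. Section 2.1 lengthens IER so that both arms receive the same restriction, yet this equation would report less restriction in IER even if every participant complied perfectly. The Discussion cites a review suggesting that refeeds may improve long-term adherence. The equation would tend to hide such a benefit, and any account of the fat-mass result in terms of adherence would start from an artefact.

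**Working it through.** **Inputs**
- Restriction days: 16 × 7 = 112 in both arms (section 2.1).
- Length of the weight-loss phase: CER 112 days; IER 23 × 7 = 161 days (section 2.1).
- Prescribed restriction: 33% of DER in restriction weeks (2.6.2), 0% in energy-balance weeks (2.6.1).
- Baseline EI = baseline EE, taking the participant to be in balance at baseline.
- *r* = EE during the phase divided by baseline EE. The Discussion expects EE to fall but gives no size, so falls of 0 to 15% are assumed.

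**The plan's own durations reproduce.** IER: 8 × 2 + 7 × 1 = 23 weeks. Whole trial: 2 + 16 + 8 + 52 = 78 weeks for CER and 2 + 23 + 8 + 52 = 85 weeks for IER, as in section 2.8.2.

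**Full compliance, EE unchanged**
- EB = −0.33 × EE × (restriction days / Δt).
- CER: 0.33 × 112/112 = 33%; adherence = 33/33 = 100%.
- IER: 0.33 × 112/161 = 22.96%; adherence = 22.96/33 = 69.6%, which is 16/23.
- Illustration with an assumed DER of 2,400 kcal/d: the deficit is 792 kcal/d in restriction weeks, and 792 × 112 = 88,704 kcal in total. Divided by 161 days this is 551 kcal/d, or 22.96% of 2,400.
- To score 100%, an IER participant would need a deficit of 33 × 23/16 = 47.4% in the restriction weeks.

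**Full compliance, EE falling**
- CER score = 100 × (1 − 0.67*r*)/0.33.
- IER score = 100 × (1 − 0.7704*r*)/0.33.
- Gap = 30.4 × *r* points.

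| Fall in EE | CER | IER, Δt = 161 d | Gap (points) | Either arm, Δt = 112 d | IER, Δt = 161 d, prescription 22.96%, baseline EI kept |
|---|---|---|---|---|---|
| 0% | 100.0 | 69.6 | 30.4 | 100.0 | 100.0 |
| 5% | 110.2 | 81.2 | 28.9 | 110.2 | 116.8 |
| 10% | 120.3 | 92.9 | 27.4 | 120.3 | 133.6 |
| 15% | 130.5 | 104.6 | 25.9 | 130.5 | 150.3 |

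The fall is in the EE value that enters the equation. A linear fall of 10% across the phase, averaged, corresponds to the 5% row.

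**Does the 4-month label change the answer?** If IER is read at calendar week 16, 11 of 16 weeks have been restricted, and full compliance with EE unchanged scores 11/16 = 68.8%. The gap stays.

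**The case against.** The strongest reply is that Δt is nowhere written as 161 days. The EI term is labelled 4 months, which fits 16 weeks and not 23 (about 5.3 months). The Fig 1 legend indexes visits by weeks of restriction (t18 for 16 weeks of restriction, ending at t78), although IER lasts 85 weeks. On that convention Δt could be 112 days in both arms, and the gap vanishes. This stands in part: the divisor is not defined by arm. But no section states a 112-day divisor, section 2.5 refers to the length of the intervention, section 2.1 gives that length as 23 weeks for IER, and the calendar reading of 4 months does not help.

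Some stronger readings are tempting but not supported:
- *Fixed scores of 70% and 100%.* These need EE to stay at baseline, which the Discussion does not expect. Only the gap is roughly stable.
- *Δt might cover all three phases, since section 2.1 calls the whole a three-phase intervention.* Section 2.5 ties the calculation to the weight-loss intervention, and section 2.6.4 to the weight-loss phase.
- *The refeed weeks cannot be checked by this method.* Section 2.6.4 promises a check of those weeks without saying that it uses body composition. Home weights, weekly calls and photo records are all planned.
- *The main results are biased.* Adherence is not a listed primary or secondary outcome, section 3.5 specifies intention-to-treat analysis and no adherence-based analysis, and the fat-mass and adaptive-thermogenesis tests do not use the formula.

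**Conclusion.** The point holds on the plain reading of sections 2.1, 2.5 and 2.6.4 together. With EE unchanged, a fully compliant IER participant scores 16/23 of the CER score, and the reported degree of restriction is about 23% against 33%. With an assumed EE fall of 0 to 15%, the same in both arms, both scores rise and a gap of about 26 to 30 points remains. The result rests on Δt being the full weight-loss phase, on energy-balance weeks being truly neutral, and on baseline intake equalling baseline EE. As written, adherence and degree of restriction cannot be compared between arms. This should be fixed before analysis; it is not critical, because no primary or secondary test depends on it.

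**What to change.** Preferred: state in sections 2.5 and 2.6.4 that body stores are measured from the start to the end of the weight-loss phase in each arm, and that Δt is the 112 prescribed restriction days in both arms. Equal compliance then gives equal scores at every EE fall in the table. Two limits should be stated. Scores still exceed 100% when EE falls, because baseline EI stays the reference while plans are reset every 4 weeks. And any imbalance in the refeed weeks is attributed to the restriction days.

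Alternative: keep the full span and use a time-weighted prescription, 33% for CER and 33 × 16/23 = 22.96% for IER. This is safe only if baseline EI is also replaced by the mean of the DER values on which the plans were based. With baseline EI kept, a 5% fall in EE gives IER 116.8% against CER 110.2%. With both changes, full compliance scores 100% in each arm, provided that measured EE agrees with those DER values. The price is a departure from the published formula that the article cites, which should be declared.

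Either option is a change of analysis wording. The body-composition, EE and DER data are already planned, and no visit or procedure is added.

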### 2.6. Nutritional intervention and estimation of energy requirements

Nutritional intervention will comprise a personalized dietary plan prescribed for each participant, considering their daily energy requirements (DER) through each phase of the intervention. The DER will be estimated by multiplying the REE measured (mREE) by a PA level (PAL) [40], in phase 1, and using REE and accelerometry data [41], in phase 2 and 3. DER will be calculated in every visit/evaluation performed during the trial (8 in total). The main investigator will be responsible for all appointments, follow-ups and diet plans, including calculation of DER.

The energy distribution by macronutrients will be 35% from protein, 35% from carbohydrate and 30% from fat in all study-phases. A Mediterranean-style diet will be prescribed for both groups, aiming for improving diet quality, and using portion control to achieve energy requirements during EB, ER and WM. The Mediterranean-style diet includes the following recommendations: high intake of vegetables including leafy green vegetables, fruits, wholegrain cereals, nuts and pulses, legumes, and extra virgin (cold pressed) olive oil; moderate intake of fish, seafood, eggs, poultry, and dairy products; low intake of red meat (less than twice a week) and red wine should be consumed in moderation [42]. Processed foods, sweets, cookies, chips, high-fat cheeses, sausages and unhealthy foods are to be avoided. The dietary plan will be adjusted when necessary, according to participant´s feedback.

#### 2.6.1. Neutral energy balance for weight stabilization

For weight stabilization, a personalized dietary plan meeting 100% of their DER will be prescribed for each participant. This dietary plan will take into consideration calculations of DER at every visit/evaluation, and will be adjusted when needed.

Participants will be provided with a digital scale on the 1^st^ visit, to track their weight daily at home [43, 44], and will be instructed to weight themselves after a 10h-overnight fast, wearing only underwear, and weekly share with the main investigator their overnight fasting body weight. During EB, if they identify a weight gain of more than 1 kg, participants will have clear instructions on how to adjust their dietary plan, in order to reduce and stabilize weight [6].

#### 2.6.2. Energy restriction for weight loss

For both groups, an ER of 33% of one’s DER will be created [6, 32] to achieve WL. Participants will have their personalized dietary plan adjusted every 4 weeks during the ER phase, according to REE measurements and PA monitoring, to assure the same energy deficit throughout this phase.

During this phase, participants will continue to track their weight daily at home [43, 44], and weekly share with the main investigator their overnight fasting body weight.

#### 2.6.3. Energy intake and diet compliance

Compliance to the dietary plan will be monitored once a week by phone, and participants will be asked to send, via social media platforms, daily photo food records during the intervention [45].

#### 2.6.4. Adherence to diet

Participants from both groups will undergo an ER meeting 33% of their DER.

Adherence will be assessed through the following equation proposed by Racette et al [46]:

$$Adherence_{\left(\%\right)}=\;100\;\times \;\left[\left(1-\frac{EI_{4mo}}{EI_{baseline}}\right)\times \;\frac{100}{ER_{prescribed\left(\%\right)}}\right]$$

Where the EI will be calculated by the “intake-balance method” [47], through changes in FM and FFM, together with total daily EE (TDEE). The following equation was used:

$${\text{EI}}_{\left(\text{kcal/d}\right)}={\text{EE}}_{\left(\text{kcal/d}\right)}+{\text{EB}}_{\left(\text{kcal/d}\right)},$$

Where EE represents the total daily EE measured by accelerometry, and EB calculated through changes in FM and FFM. The degree of ER during the WL phase will also be calculated through this equation. It will be also assessed if participants from IER group not only accomplished the prescribed ER but also if underwent the 1-week periods of neutral EB.

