According to Byrne and colleagues [6, 25, 71], adaptive responses to ER and WL can be reversed by a 7-to-14-day period of EB after, in adults with overweight or obesity. In “MATADOR” Study, a IER using a 2-week EB periods improved WL efficiency compared with CER, being AT only found in CER group, despite the lower WL and FM loss [6]. In review by Peos and colleagues [21], it was stated that “refeeds” with at least 7 days attenuate the adaptive responses to longer-term periods of ER, potentially by attenuating the reductions in EE. Furthermore, these authors also mentioned that adopting refeed periods in IER may provide a mental break from extended periods of ER, leading to a higher long-term adherence to the dietary plan compared to CER. Therefore, we also anticipate a major weight and FM loss in IER group, comparing to CER, with a greater retention of FFM, reducing therefore AT [6, 23, 30], due to the inclusion of 7-day breaks to restore EB every 2-weeks of ER, which can minimize the compensatory mechanisms associated with ER and WL, such as changes in appetite-related hormones [24] and some behavioral compensations such as increases in sedentary behavior [26].

During WL phase, we expect to find a reduction in all EE components, as usually seen during ER, namely REE and non-resting EE (spontaneous PA (SPA), non-exercise PA (NEPA), and exercise PA (EPA)) [72].

WL usually causes a reduction in thyroid hormones (T3 and T4), insulin and leptin, increasing appetite [7, 73], and causes an increase in cortisol, which reduces EE [22]. We expect to find a lower reduction in insulin, leptin, thyroid T3 and T4, as well as a lower increase in cortisol in IER, comparing to CER. The minimization of these compensatory adaptations can be explained by the 1-week EB every 2-weeks of ER. After ER intervention, we anticipate a successful WL maintenance in both groups, possibly greater in the IER group, as well as a lower AT.

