The BREAK Study focuses not only in reducing energy intake through portion control, but also in improving nutritional quality of the diet, by increasing fruit and vegetable intake, and decreasing processed and energy-dense foods. Participants will be educated and encouraged to daily monitor their behavior, weight, and eating pattern, leading to self-efficacy for diet and WM, which are determinants of WL maintenance [66]. Although maintaining high levels of PA has been pointed out as a determinant of WL maintenance [74], the BREAK Study is a diet-only [75] intervention. Therefore, no PA recommendations will be given to participants throughout the WL and WM phases.

One of the strengths of The BREAK Study is the 2-week baseline EB for determining energy requirements, stabilizing weight, and adapting participants to the prescribed dietary plan. Another strength is the determination of REE and PA monitoring every 4 weeks of ER, allowing adjustment of the dietary plan to ensure the energy deficit of 33% during the 16-week ER phase. Monitoring AT-related hormone changes during WL and WM is also a strong point of this study, enabling a better understand of AT in both groups.

However, some limitations should be addressed, such as: i) the nutritional intervention occurs in a free-living scenario, with no food being delivered to participants, preventing a valid assurance that participants are in fact consuming the prescribed energy. To minimize this adherence limitation, participants are instructed to weekly share with the main investigator their overnight fasting body weight and photo records of their meals; ii) a large interindividual variability in PAEE is expected and may not be accurately detected by accelerometry; iii) the eventual more than expected drop out of the study, due to its length, possibly weakening the statistical power of the analysis.

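### Adherence is scored against fixed baseline intake while the prescription is re-set to current needs, so exact compliance scores above 100% once energy expenditure falls

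*Protocol article*

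**What the plan says.** Section 2.6.4 defines adherence as 100 × [(1 − intake at 4 months / intake at baseline) × 100 / prescribed restriction in %]. The intake ratio appears in the formula's source text as "EI_{4mo}}{EI_{baseline". Intake (EI) is to be derived by the intake-balance method, "through changes in FM and FFM, together with total daily EE (TDEE"), as EI = EE + EB, where EB is the energy balance. No separate rule is given for baseline intake.

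The prescription is described elsewhere in the article:

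- Section 2.6.2: "an ER of 33% of one’s DER will be created", and "Participants will have their personalized dietary plan adjusted every 4 weeks during the ER phase, according to REE measurements and PA monitoring".
- Section 2.6: "DER will be calculated in every visit/evaluation performed during the trial (8 in total").
- Section 4 lists as a strength the 4-weekly re-measurement, "allowing adjustment of the dietary plan to ensure the energy deficit of 33% during the 16-week ER phase".

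Section 4 also states the expected course of expenditure: "During WL phase, we expect to find a reduction in all EE components".

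**The concern.** The reference in the score is fixed at baseline, while the target follows current needs. If needs fall, intake 33% below current needs is more than 33% below baseline, and the formula credits the difference as adherence. The score then mixes two things: how closely the woman kept to her plan, and how far her expenditure fell.

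This matters because section 4 names free-living intake, with no food supplied, as a limitation. A reader who wants to know whether a fat-mass difference reflects the break pattern or different compliance will look at this score. Energy expenditure is also part of what the trial studies, so the adherence measure should not depend on it.

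A second issue is conditional. If baseline intake is itself derived by intake-balance, the only interval before restriction is the 2-week run-in. A body-composition change measured with error would then be divided by only 14 days and placed in the denominator.

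**Working it through.** **Inputs from the article.** Prescribed restriction 33% (2.6.2). Energy densities 9.5 kcal/g for fat mass (FM) and 1.0 kcal/g for fat-free mass (FFM) (2.5). Run-in 2 weeks = 14 days. Restriction 16 weeks = 112 days in both arms, spread over 23 calendar weeks in the intermittent arm (IER) (2.1).

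**Assumptions.** Baseline intake equals baseline EE. EE falls by d = 5, 10 or 15%; the article gives the direction but no size.

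**Anchor.** With no fall, full compliance means intake of 0.67 × baseline, and the score is 100 × (1 − 0.67)/0.33 = 100%. The formula is right when needs are constant.

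**Drift.** With needs at (1 − d) of baseline, exact compliance gives intake of 0.67(1 − d), so

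score = 100 × [1 − 0.67(1 − d)]/0.33.

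Each 1% fall adds 0.67/0.33 = 2.03 points. If expenditure is averaged over a linear fall, d is replaced by d/2.

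| Case | d = 5% | d = 10% | d = 15% |
|---|---|---|---|
| Exact compliance, phase-average EE | 105.1 | 110.2 | 115.2 |
| Exact compliance, end-of-phase EE | 110.2 | 120.3 | 130.5 |
| Half compliance (16.5% below current needs), end-of-phase | 62.7 | 75.3 | 88.0 |
| No current deficit, end-of-phase | 15.2 | 30.3 | 45.5 |
| Current deficit (%) that scores 100, 1 − 0.67/(1 − d) | 29.5 | 25.6 | 21.2 |

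If section 2.6.2 is read as holding a constant kcal deficit, exact compliance means intake of (1 − d) − 0.33. End-of-phase scores are then 115.2, 130.3 and 145.5%. The direction is the same.

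The table lets the plan track needs without lag. With re-setting at weeks 0, 4, 8 and 12, the average fall built into the plan is (0 + 0.25 + 0.5 + 0.75)/4 = 0.375 of d instead of 0.5. The phase-average scores become 100 + 2.03 × 0.375 × (5, 10, 15) = about 104, 108 and 111%.

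**Conditional point on baseline noise.** Suppose baseline intake uses the FM and FFM change over the run-in. A given error then has 112/14 = 8 times the per-day effect it has over the restriction phase. Assume a per-measurement FM error SD of 0.3 to 0.7 kg, an equal and opposite FFM error (net 9.5 − 1.0 = 8.5 kcal/g) and total daily EE (TDEE) of 2200 kcal/d:

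- 0.3 kg: 8.5 × 300 × √2/14 = 258 kcal/d; 258/2200 × 2.03 = about 24 points.
- 0.7 kg: 8.5 × 700 × √2/14 = 601 kcal/d; 601/2200 × 2.03 = about 55 points.

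These are SDs of one woman's score from the denominator alone.

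**Averaging interval in IER.** If EB is averaged over all 23 weeks, a fully compliant woman has a mean deficit of 16 × 33/23 = 23.0% and scores 23.0/33 = 69.6%, before any fall in EE. Replacing the baseline reference by concurrent expenditure does not cure this unless restriction days are counted explicitly.

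**The case against.** Several counter-arguments have force.

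- **The score need not rise whenever EE falls.** Correct: at unchanged absolute intake it does not move. The drift arises at a given degree of compliance with the re-set plan, which is what the score is meant to measure.
- **The larger figures are an upper version.** Section 2.5 defines EB as an average over the intervention. If EE is averaged as well, the excess is halved. It does not vanish.
- **Baseline intake may simply be measured EE.** The run-in is prescribed at neutral balance and section 2.6.4 names no baseline window, so this reading is as natural as the other. The noise of 24 to 55 points would then disappear; the drift would remain.
- **Other checks exist.** There are weekly calls and photo records (2.6.3), and section 2.6.4 adds a degree of restriction during weight loss and a check on the break weeks. The degree of restriction might already be the concurrent measure, but its reference is not stated.
- **Consequence is limited.** Adherence is neither a primary nor a secondary outcome. Section 3.5 makes all analyses intention-to-treat and names no adherence-adjusted analysis. This stands.

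A reader might infer that the score favours continuous restriction (CER), because the trial expects more adaptive thermogenesis there. Taken alone, the 209 kJ/d (50 kcal/d) quoted in section 1 for the CER arm of the earlier trial in men would add 50/2500 to 50/2000 × 2.03, or about 4 to 5 points, at an assumed TDEE of 2000 to 2500 kcal/d. The article does not support that direction. In the same trial the intermittent arm lost more weight (about 12.9% against 8.4%), and section 4 expects greater weight and fat loss in IER here. Greater tissue loss lowers EE in IER and acts the opposite way.

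**Conclusion.** The mismatch is real and follows from the article's own formula and re-set rule. It is not a detail left to an analysis plan, because the formula is stated explicitly. Under the stated assumptions, exact compliance is overstated by about 5 to 15 points with phase-average EE and 10 to 30 with end-of-phase EE, for EE falls of 5 to 15%. The 4-week steps trim the phase-average excess by a quarter. Partial adherence is overstated as well.

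The size of the fall is assumed. No direction of bias between arms can be claimed. The noise in the denominator is a risk only if baseline intake is derived from the 14-day change. No primary or secondary outcome analysis is altered, so this is a correction worth making to a supporting measure and not a threat to the main comparison.

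**What to change.** Define the main adherence score as achieved cumulative deficit over prescribed cumulative deficit:

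adherence (%) = 100 × (−EB × days in the interval) / (0.33 × mean TDEE over the restriction-phase visits × 112).

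The interval is the whole active phase, 16 weeks in CER and 23 in IER. The prescribed restriction days are 112 in both arms, so break weeks are not counted as restriction. With a plan that tracks needs and break weeks in balance, full compliance scores 100% in both arms at any EE fall. Allowing for 4-week steps and a linear fall in the CER arm, it scores [(1 − d/2) − 0.67(1 − 0.375d)]/[0.33(1 − d/2)] = about 99, 97 and 96% for falls of 5, 10 and 15%, compared with 104, 108 and 111% under the stated formula.

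Keep the published baseline-referenced formula as a secondary description. State how baseline intake is obtained for it and over which window, and state the reference for the degree of restriction.

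The cost is a rewritten definition. REE, accelerometry and body composition are already collected, and no dietary rule changes. The downside is less direct comparability with earlier studies that used the published formula.
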